### **7.4.2 Post- Primary Outcome - Antiretroviral Therapy Follow-up Visits**

Prior to being started on self-administered ARV therapy and entry to STEP 3, a pre-ARV baseline evaluation will be completed; this will include the following examination (appendix I, Step 3):

1. HIV RNA Roche Amplicor
2. Quality of life assessment
3. Plasma storage
4. PBMC storage/ immune function (Flow cytometry to assess cell surface activation markers, EliSpot to assess CD4 and CD8 T cell specificity to HIV and microbial peptides, Whole blood assays to determine antigen specific response to HIV and microbial antigens)

Assessments from confirmation of study outcome, or ARV safety evaluation may be used for pre-antiretroviral baseline if they were completed within two weeks before ARV baseline.

Patients will then be started on self-administered, ARV therapy and enter STEP 3 (Section 5.0 describing the initiation of therapy). Patients will receive detailed counseling about treatment with antiretroviral therapy. They will be informed that adherence measures will be made including unannounced home visits to record self-reported adherence and pill counts. Below is the schedule for STEP 3:

1. Medical history and physical examination including weight (Week 2, months 1, 2, 3, 6, 9, 12, 15, 18, 21, 24, 27, 30, 33, 36, and then every 4 months or as clinically indicated)
2. Adverse experiences survey (Week 2, months 1, 2, 3, 6, 9, 12, 15, 18, 21, 24, 27, 30, 33, 36, and then every 4 months or as clinically indicated)
3. New diagnoses and/or hospitalizations since the last study visit (Week 2, months 1, 2, 3, 6, 9, 12, 15, 18, 21, 24, 27, 30, 33, 36, and then every 4 months or as clinically indicated)
4. Urine or serum -HCG pregnancy test (if suspect)
5. CD4+ lymphocyte count (months 3, 6, 12, 18, 24, 30, 36, then every 4 months thereafter or as clinically indicated)
6. CBC with differential and platelet count (months 3, 6, 12, 18, 24, 30, 36, then every 4 months thereafter or as clinically indicated)
7. Posterior-anterior chest X-ray (as clinically indicated)
8. Sputum semi-quantitative AFB smear and culture on solid media X 2 (as clinically indicated)
9. MTB drug susceptibility (as clinically indicated)
10. Serum aspartate aminotransferase (AST), serum bilirubin (months 1, 2, 6, 12, 18, 24, 30, 36, and every 4 months thereafter or as clinically indicated)
11. Serum creatinine (as clinically indicated)
12. Plasma HIV RNA level (months 1, 2, 3, 6, 12, 18, 24, 30, 36, and every 4 months thereafter or as clinically indicated)
13. Adherence Questionnaire (antiretroviral therapy) (months 1, 2, 3, 6, 9, 12, 15, 18, 21, 24, 27, 30, 33, 36, and then every 4 months or as clinically indicated)
14. Quality of life assessment (months 6, 12, 18, 24, 30, and 36)
15. Plasma storage (months 1, 2, 3, 6, 12, 18, 24, 30, 36, and every 4 months thereafter, or as clinically indicated)
16. PBMC storage/ immune function (month 3 and 6, or as clinically indicated)
17. HIV RNA genotyping (as clinically indicated)
18. Store MTB isolate for DNA fingerprinting (All isolates from positive cultures of suspected relapse cases will be stored at -70° C for DNA finger printing with the patient’s initial isolate, as clinically indicated)
19. Disease-specific evaluation per WHO staging system (as clinically indicated)

## 7.5 Sick Visit Evaluation

At any point during the study (Steps 1, 2, or 3), study patients will be encouraged to seek medical care for intercurrent illness or medical condition. At these sick visits, evaluation may as clinically indicated include the following:

1. Interim history and physical exam including vital signs, concomitant medications, adverse experiences, and major TB and HIV-related signs and symptoms
2. New diagnoses and/or hospitalizations since the last study visit
3. Sputum semi-quantitative AFB smear and culture on solid media X 2
4. Adverse experience survey
5. CBC, differential white blood cell and platelet count
6. Serum aspartate aminotransferase (AST), serum bilirubin
7. Urine or serum -HCG pregnancy test (females of child bearing potential only)
8. Posterior-anterior chest X-ray
9. Plasma HIV RNA level
10. Serum creatinine
11. Adherence Questionnaire (TB or antiretroviral therapy)
12. Disease-specific diagnostic tests (Appendix II, WHO Staging Criteria
13. CD+4 lymphocyte count
14. Store MTB isolate for DNA fingerprinting (All isolates from positive cultures of suspected relapse cases will be stored at -70° C for DNA finger printing with the patient’s initial isolate)
15. Plasma storage
16. PBMC Storage

# 8.0 CLINICAL MANAGEMENT

## 8.1 HIV

### **8.1.1 Disease Management**

Management of HIV related complications and the prophylactic use of Septrin will be in line with a manual of Ugandan standard-of-care guidelines or the guidelines of the Ministry of Health, whichever is most recent.64 These guidelines provide recommended treatment and management of common fungal (oral and esophageal candidiasis, cryptococcal meningitis), viral (herpes simplex, HHV-8), and bacterial (pneumococcal pneumonia, sinusitis, etc.) complications of HIV. Because of high CD4+ cell count and the use of potent ARV, we will be prepared, but do not expect, to manage large numbers of opportunistic infections in this cohort during the Intervention Period. Laboratory facilities are available on-site for diagnosis of the most common infections including candida, cryptocococcal disease, bacterial infections, viral complications (HSV and VZV), and HIV-associated malignancies (Kaposi sarcoma, lymphoma, etc.). When women become pregnant during follow-up, they will be referred to the Uganda national Nevirapine implementation program for management of the pregnancy and delivery (Section 8.3)

### **8.1.2 Toxicity Management**

#### **8.1.2.1 General Guidelines for Adverse Experiences Associated with HIV and ARV**

#### **Therapy**

##### 8.1.2.1.1 Grades 1 and 2

Subjects who develop a Grade 1 or 2 adverse event or toxicity may continue study drugs without alteration of the dosage, except **as stated in the following sections**.

In general, for grade 1 toxicities, the patient should be followed carefully, and the study drug should be continued. The patient will receive specific counseling about the observed toxicity and will be instructed on what to do if symptoms worsen. For grade 2 toxicities, the patient should be followed carefully, with additional laboratory and/or clinic appointments as clinically indicated, and the study drug or combination held at the local clinician’s discretion until the event has resolved. The clinician should also evaluate concomitant medications to determine whether to withhold or discontinue the study drugs. Guidelines for the discontinuation of study drug is given in (Section 8.1.4.2).

Grade I and II events will be reported on standard case report forms.

##### 8.1.2.1.2 Grades 3 and 4

For any grade III or IV adverse event or toxicity, the offending agent(s) or all potential causative agents will be held pending evaluation. When clinically indicated, concomitant medications should be held first if the local clinician suspects they are contributing to the toxicity. In many instances, however, all study drugs will be discontinued at once to reduce risk to the patient. The on-site clinical coordinator will report the grade IV events to the study investigators and the Data and Statistical Center within 24 hours using standard procedures; the Data and Statistical Center will be responsible for reporting the grade IV event to the study sponsor. Grade III and IV adverse events and toxicities as defined by the Study Toxicity Tables (Appendices IV and V) and occurring during study therapy or within 60 days of the last study dose must be documented as Adverse Events. The standard reporting level for adverse events will be followed, reporting only grade IV events to the Division of AIDS.

Once a grade III or grade IV adverse event is suspected, the clinician(s) on-site should begin a diagnostic evaluation to determine the cause, or potential cause, of the observed event. If the grade III/IV adverse event is caused by hypersensitivity to the study drug, then the drug will be discontinued and appropriate substitutions made. If the adverse event (not a hypersensitivity reaction) has been caused by one or more of the study drugs, then offending agent(s) will be held until the adverse event has resolved to grade II or less. In general, for symptomatic grade III/IV events, the medication will be discontinued (see Section 8.1.4) and appropriate substitutions made (Section 5.2.1.4). For asymptomatic grade III/IV events, rechallenge with the study drug is allowed after resolution of laboratory values except for toxicities as outlined in the following section (8.1.2.2). If the investigator has compelling evidence that the adverse event has NOT been caused by the study drug, dosing may continue when the adverse event has resolved. If the event recurs within 4 weeks of rechallenging with the study drug, it must be discontinued.

#### **8.1.2.2 Antiretroviral Therapy Toxicity and Management**

Patients will be closely monitored for signs and symptoms of study drug toxicity. For all toxicities that require either temporary or permanent discontinuation of study therapy, relevant clinical and laboratory tests will be obtained as clinically indicated until final resolution or stabilization of the toxicity. Symptoms and laboratory findings will be graded by severity using the NIAIDS/ACTG Toxicity Tables (Appendices IV and V).

The study will use antiretroviral medications that have known and well-described toxicity profiles. The diagnosis and management of the major adverse events and toxicities are described below:

##### 8.1.2.2.1 Nausea (with or without vomiting)

Nausea following initiation of therapy with antiretroviral medications usually subsides or resolves during the first few weeks of treatment. With the onset of Grade >1 nausea, patients will be advised to take study drugs with food. With Grade >1 nausea, subjects may be treated as needed with antiemetics given orally or by suppository.

If the nausea is considered related to ZDV and is treatment limiting in the opinion of the site investigator, allowable drug substitution should be considered.

If nausea persists despite food and antiemetics or increases in severity, interrupt drug therapy. Once nausea resolves, therapy must be resumed using the full doses of study drugs, with the exception of the ZDV dose reduced to 200 mg BID. The dose will be increased as tolerated thereafter. If intolerable nausea recurs following resumption of therapy, protocol-allowable drug substitution(s) should be considered.

##### 8.1.2.2.2 Anemia/Neutropenia

Anemia and neutropenia are recognized toxicities of ZDV. In subjects with Grade 1 anemia, the study medications will be continued and the CBC monitored until resolution or until the anemia worsens. Subjects with Grade 2 anemia considered treatment limiting by the on-site investigators may have the ZDV dose reduced to 200 mg BID, to determine if the anemia or neutropenia resolves. If it does not resolve, protocol-allowable drug substitution(s) will be made. Modifications of ZDV will involve the use of a separate preparation instead of the fixed dose combination contained in Combivir.

Subjects with Grade >3 anemia or neutropenia attributed to ZDV may have treatment interrupted until the adverse experience has returned to Grade <2. Once the anemia or neutropenia has returned to Grade <2, ZDV may be restarted at a lower dose of 200 mg BID, to determine if the anemia or neutropenia recur. At the discretion of the site, the ZDV dose may be re-escalated as tolerated. If the toxicity does not resolve, then discontinue ZDV and substitute with suitable ARV.

Severe anemia will be managed with blood transfusions when the hemoglobin drops below 7 mg/dl.

Should a subject experience toxicity resulting from the fixed dose combinations of 3TC/ZDV, then the individual formulations of ZDV 300 mg tablet, or 3TC 150 mg tablet will be given separately with an appropriate dose reduction. Where necessary, protocol-allowed substitution(s) will be performed after discussions with the study investigators.

##### 8.1.2.2.3 Adverse Experiences to Abacavir (ABC)

ABC Hypersensitivity Reactions (HSRs) - *Background*

In clinical studies, approximately 3%-5% of patients receiving ABC develop an HSR that in rare cases has proved fatal. HSR is characterized by the appearance of symptoms indicating multiorgan/body system involvement. Symptoms usually appear within the first 6 weeks of starting treatment with ABC (median time to onset is 11 days), but may occur at any time while on therapy, and most often include fever, rash, gastrointestinal symptoms (nausea, vomiting, diarrhea, or abdominal pain), respiratory symptoms (dyspnea, sore throat, cough), and lethargy or malaise. Other signs and symptoms may include musculoskeletal symptoms (myalgia, rarely myolysis, arthralgia), headache, paresthesia, and edema. Respiratory tract symptoms (dyspnea, sore throat, cough) have been observed in approximately 20% of subjects who experience HSR.

The diagnosis of hypersensitivity to ABC remains a clinical diagnosis. There is no pathognomonic clinical sign or laboratory finding that renders the diagnosis. The key feature is that HSR is a multi-organ system reaction. Some patients with HSRs were initially thought to have respiratory tract disease (pneumonia, bronchitis, pharyngitis) or a flu-like illness. The multisystem nature of the HSR has led to misdiagnosis of the HSR as an intercurrent medical illness or as being related to another medication. HSR also has been unrecognized when it presents with less common symptoms or as a single symptom.

This misattribution of the symptoms of HSR to another medical condition or delay in diagnosis of hypersensitivity has resulted in ABC being continued or reintroduced, leading to more severe or rapid (within hours) onset of HSR or death. Therefore, the diagnosis of HSR should be carefully considered for patients presenting with symptoms of these diseases, even if another medical diagnosis seems likely. Renal failure and anaphylaxis have also been reported in association with HSRs. Reintroduction of ABC in subjects after treatment interruption, with no preceding symptoms of HSR, has, rarely, resulted in HSR. Given the risk profile of ABC, ABC therapy SHOULD NOT be restarted following an HSR, because more severe symptoms will occur within hours and may include life-threatening hypotension and death. Subjects who develop signs or symptoms of hypersensitivity should discontinue treatment as soon as an HSR is first suspected and should seek medical evaluation immediately, preferably on the same day that symptoms are reported.

Physical findings may include lymphadenopathy and, occasionally, mucous membrane lesions (conjunctivitis and/or mouth ulceration) and hypotension. The rash is variable and may be absent, but often appears maculopapular or urticarial. Laboratory abnormalities that may accompany ABC hypersensitivity include elevated liver function tests (LFTs), creatine kinase, or creatinine or lymphopenia.

Symptoms related to this HSR worsen with continued therapy and usually resolve upon discontinuation of ABC. Restarting ABC following an HSR results in a prompt return of symptoms within hours. This recurrence of the HSR may be more severe than on initial presentation and may include life-threatening hypotension and death.

ABC HSR - *Diagnosis of HSR*

The clinical diagnosis of suspected HSR is described in Section 6.3.1.2.1. Hypersensitivity Reaction associated with Abacavir.

*ABC HSR - Management of HSR*

If the clinical team makes the diagnosis of suspected HSR according to the standard definitions, then ABC will be held and discontinued when the diagnosis is confirmed by the resolution of symptoms. Patients with suspected HSR will be placed on the ‘ABC HSR Evaluation and Follow-up Protocol’. This protocol will involve complete initial diagnostic evaluation as described above, close follow-up with detailed evaluations by study physicians until all symptoms resolve or until an alternative diagnosis is established. Each patient placed on this protocol will be reviewed by experienced study clinicians and discussed with the senior study investigator at the point of patient contact. The information collected during this follow-up period will be recorded on a standard clinical report form for later review and classification.

In some cases of suspected HSR, the signs and symptoms consistent with ABC HSR may be mild or attributed to an intercurrent medical illness. In these cases, on-site physicians may decide to continue the ABC while monitoring signs and symptoms closely for any further development of ABC HSR. This decision will only be made after consulting senior investigators on the study at the point of patient contact. If signs or symptoms evolve, or HSR cannot be ruled out, ABC will be discontinued, even when other diagnoses are possible or likely (e.g., respiratory tract infections, gastroenteritis, or adverse events related to another drug).

In cases where the diagnosis of ABC HSR is strongly suspected, the patient will be instructed to hold all antiretroviral medications including ABC pending further evaluation. If signs and symptoms of ABC HSR resolve after discontinuing the medication, then the clinical diagnosis will be established, and ABC will be discontinued. The patient will be started on a protocol-allowable substitution regimen. The patient will be instructed to return unused ABC medication or combinations containing ABC to the clinic. The patient will be advised that they should never take ABC again, as life-threatening HSR may occur.

The clinical presentation and severity of the HSR will dictate the supportive care offered to patients with HSR. In the most severe cases, patients will be hospitalized for 24 hours on the Tuberculosis Ward 5/6 of Mulago hospital for observation. Supportive care will be given and will include intravenous fluids for hypotension, treatment of alternative diagnoses, antipyretics, and symptomatic and/or supportive treatment as indicated. Although there are no clinical data demonstrating the benefit of antihistamines or corticosteroids in the management of hypersensitivity, they will be used in severe cases. In mild or moderate cases, without unstable vital signs, the medication will be stopped and the patient observed in the clinic for several hours. These patients will be taken home by home visitors and seen in follow-up the following day.

All clinical data obtained will be reported on the relevant case report forms (CRF), and the event “ABC hypersensitivity” is to be reported as a serious adverse event on the Division of AIDS, Regulatory Control Center Safety Office, SAE form. In addition, the **GlaxoSmithKline’s** “Abacavir Hypersensitivity Reaction Adverse Event Record” should be completed and returned to **GlaxoSmithKline** per the instructions on the form.

*ABC HSR - Fever*

The onset of fever may herald hypersensitivity. If HSR is suspected, then patients will be placed on the HSR Evaluation and Follow-up Protocol. In the event of a clinical presentation consistent with hypersensitivity, ABC should be held until evaluated by a study doctor, as described above.

*Toxicity Management for ABC/3TC/ZDV Tablets*

Should a subject experience toxicity resulting from the fixed dose combinations of ABC/3TC/ZDV or 3TC/ZDV, administer the individual formulations of ZDV 300 mg tablet, 3TC 150 mg tablet and/or ABC 300 mg tablet simultaneously and dose reduce or make protocol-allowed substitution(s), if necessary with permission from the protocol chairs. If a subject experiences an ABC HSR, discontinue ABC permanently.

##### 8.1.2.2.4 CNS and Psychiatric Symptoms with Efavirenz (EFV)

Subjects will be informed that CNS symptoms may occur with EFV. These symptoms include serious psychiatric symptoms (e.g., depression) and CNS symptoms (e.g., dizziness, impaired concentration, insomnia, bad dreams, etc.). Patients will be informed that these symptoms are likely to improve with continued therapy. Dosing at bedtime improves the tolerability of these symptoms and is recommended during the first weeks of therapy and in subjects who continue to experience these symptoms. Subjects receiving EFV should be alerted to the potential for additive CNS effects when EFV is used concomitantly with alcohol or psychoactive drugs. For patients taking rifampin, dose reduction from 800-mg to 600-mg QD EFV is allowed if CNS symptoms persist.

Subjects also should be informed that EFV may cause dizziness, impaired concentration, and/or drowsiness and instructed that if they experience these symptoms they should avoid potentially hazardous tasks such as driving or operating machinery.

There have been reports of delusions and inappropriate behavior, predominantly in subjects with a history of mental illness or substance abuse. Severe acute depression (including suicidal ideation/attempts) has also been infrequently reported in both EFV-treated and control-treated subjects. Subjects who experience these symptoms should contact their doctor immediately because discontinuation of EFV may be required.

##### 8.1.2.2.5 Pregnancy with Efavirenz (EFV) or Abacavir (ABC)

If a subject becomes pregnant while on study, she must inform the study personnel and will be referred to appropriate antenatal clinic for the pregnancy. If she is on Trizivir, she may continue the medication for the duration of her pregnancy. If the patient is on EFV, she must discontinue it immediately and may replace it with nevirapine, if she chooses. Nevirapine cannot be used if the patient has CD4>250. For pregnant women with CD4>250, the antiretroviral regimen will be considered on a case-by-case basis by the study investigators.

##### 8.1.2.2.6 Rash with Efavirenz or Nevirapine

In the event that a subject experiences rash (with or without systemic symptoms), he/she should be evaluated for the possibility of an ABC or NVP HSR, for cutaneous adverse events associated with EFV or NVP. Subjects who experience rash during the first 2 weeks of NVP treatment must not increase the dose of NVP until the rash resolves.

For Grade 2 rash, antihistamines or topical corticosteroids may be prescribed. Subjects may continue all study drugs. The subject should be advised to contact the physician immediately if there is any worsening of the rash, or if systemic signs or symptoms develop that could be compatible with an HSR. It is extremely important to closely monitor the subject, especially if EFV or NVP has been interrupted because of rash, to ensure that symptoms do not worsen or that signs or symptoms consistent with clinical hepatitis or with hypersensitivity to ABC or NVP do not develop. Women appear to be at higher risk of NVP rash than men. All subjects developing a rash, at any time during NVP treatment, but particularly during the first 20 weeks, should have LFTs performed at that time. After the initial 20-week period, frequent clinical and laboratory monitoring should continue throughout NVP treatment.

Subjects developing signs or symptoms of severe skin reactions or HSR must be advised to discontinue NVP and seek medical attention immediately. Assess rash and evaluate ALT/AST. If severe rash OR rash with constitutional symptoms of organ dysfunction OR rash and increased ALT or AST occurs, then permanently discontinue NVP. If urticarial rash (mild or moderate) occurs, the subject may continue NVP, but DO NOT reintroduce NVP if it is stopped. For severe or generalized urticarial rash, NVP must be permanently discontinued.

EFV or NVP may be held at the investigator’s discretion until the cutaneous toxicity returns to Grade <1, at which time EFV therapy should be reinstituted at full dose. If NVP is held > 7 days, NVP should be reinstituted with the lead-in dose of 200 mg QD for 2 weeks, then 200 mg BID. If a Grade 2 cutaneous/allergic reaction recurs, the medical officer should discuss with the study investigators whether the subject should be further re-challenged. The subject should be closely monitored for recurrence of the rash, HSR, clinical hepatitis, or isolated changes in LFTs. If any of these conditions develop on NVP, the subject should immediately and permanently discontinue NVP. For subjects on NVP, if resolution takes more than 2 weeks, contact the study investigators.

If the rash is considered to be most likely due to concomitant illness or medication, standard management, including discontinuation of the likely causative agent, should be undertaken. If no other causative factor is found after clinical evaluation, the subject should be treated symptomatically until the rash resolves.

For Grade 3 rash, subjects should hold all study drugs.Upon resolution to Grade <1, the investigator should discuss at a study conference call with senior investigators whether re-challenge is appropriate. If the Grade 3 rash is considered to be most likely due to concomitant illness or medication, standard management, including discontinuation of the likely causative agent, should be undertaken.

For Grade 4 rash, (e.g., exfoliation, mucosal involvement, or target lesions [erythema multiforme]) or any evidence of Stevens-Johnson syndrome, subjects should discontinue all study drugs.

For grade ≥ 3 rash, do not substitute EFV for NVP or NVP for EFV

In the event that Grade 2 or 3 rash fails to resolve after 14 days, increases in severity, is associated with systemic (fever, malaise, nausea) or allergic (e.g., urticaria) symptoms, or is associated with mucosal or target lesions, all study drugs should be held until symptom resolution. NVP has been rarely associated with the development of severe rash, including SJS and toxic epidermal necrolysis (TEN). A new onset prodromal syndrome consisting of clinical symptoms manifested as fever (>39°C), malaise, cough, lymphadenopathy, edema, myalgia, and/or arthralgia may occur prior to the development of cutaneous manifestations of SJS, TEN, or the SJS/TEN overlap syndrome.

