##### 8.1.4.2.3 Criteria for Re-starting Antiretroviral Therapy

The decision to restart antiretroviral therapy will depend on the type of adverse event and the study drug. Three general situations will arise:

1. If a patient develops intolerance to a medication as evidenced by an adverse event, then the medication(s) may be re-started once the adverse event has resolved or subsided to a grade II reaction or less. In this setting, the offending medication may be restarted under close supervision that involves direct observation of the initial dose and frequent clinical and laboratory monitoring thereafter.
2. If a patient develops an allergic or hypersensitivity reaction to one or more of the antiretroviral medications, the drug(s) must be discontinued and NOT be re-started. See comments below regarding ABC.
3. If a patient develops an adverse event to a medication other than an antiretroviral medication, then the antiretroviral medications may be re-started under careful clinical supervision.

Study medical officers and physicians have the option of substituting a protocol-approved antiretroviral medication when clinically indicated instead of re-starting medication.

*ABC – Re-Starting Therapy*

Although patients may develop allergic reactions to any medication, special rules about stopping and re-starting ABC are needed because of ABC HSR.

If the diagnosis of ABC HSR is made, then the ABC must be discontinued. If ABC was held for evaluation of an adverse event, and that adverse event is clearly ascribed to another cause, then medical officers may re-start ABC under direct observation of medical personnel and close follow-up. If ABC is to be re-started under these circumstances, the drug must be restarted by the site principal investigator or his physician designee after discussion of the risks and benefits of restarting the drug with the subject. Reintroduction of the drug must occur in Mulago Hospital where the subject can readily access medical care.

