**ESTIMATING SEVERITY GRADE**

For abnormalities NOT found elsewhere on the Tox Table, use the scale below to estimate grade of severity:

**GRADE 1 Mild** Transient or mild discomfort; no limitation in activity; no medical intervention/therapy required

**GRADE 2 Moderate** Mild to moderate limitation in activity - some assistance may be needed; no or minimal medical intervention/therapy required

**GRADE 3 Severe** Marked limitation in activity, some assistance usually required; medical intervention/therapy required, hospitalizations possible

**GRADE 4 Life-** Extreme limitation in activity, significant assistance

**threatening** required; significant medical intervention/therapy required, hospitalization or hospice care probable

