**PARAMETER GRADE 1 GRADE 2 GRADE 3 GRADE 4**

MILD MODERATE SEVERE POTENTIALLY LIFE THREATENING

Neuro-sensory Mild impairment (dec Mod impairment (mod Severe impairment Sensory loss involves

sensation, e.g., dec sensation, e.g., (dec or loss of limbs and trunk.

vibratory, pinprick, vibratory, pinprick, sensation to knees or

hot/cold in great toes) hot/cold to ankles) wrists) or loss of

in focal area or and/or joint position sensation of at least

symmetrical distri- or mild impairment mod degree in multiple

bution that is not different body areas

symmetrical (i.e., upper and lower

extremities)

URINALYSIS

Proteinuria

Spot urine 1+ 2 - 3+ 4+ Nephrotic syndrome

24 hour urine 200 mg-1 g loss/day OR >1 - 2 g loss/day OR >2 - 3.5 g loss/day OR Nephrotic syndrome OR

<0.3% OR 0.3 - 1.0% OR >1.0% OR >3.5 g loss/day

<3 g/l 3 - 10 g/l >10 g/l

Gross Hematuria Microscopic only Gross, no clots Gross plus clots Obstructive OR

transfusion req

MISCELLANEOUS

Fever 37.7 - 38.5C OR 38.6 - 39.5C OR 39.6 - 40.5C OR >40.5C OR

oral >12 hours 100.0 - 101.5F 101.6 - 102.9F 103 - 105F >105F

Headache Mild; no Rx req Mod; or non-narcotic Severe; OR responds to Intractable; OR requiring

analgesia Rx initial narcotic Rx repeated narcotic Rx

Allergic Reaction Pruritus without Localized urticaria Generalized urticaria Anaphylaxis

rash angioedema

Cutaneous/Rash/ Erythema, pruritus Diffuse maculopapular Vesiculation OR moist ANY ONE: mucous membrane

Dermatitis rash OR dry desquamation OR involvement, suspected

desquamation ulceration Stevens-Johnson (TEN),

erythema multiforme, necrosis req surgery/ exfoliative dermatitis

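### Section 8.1.2.2.6 gives incompatible nevirapine instructions for severe rash and for moderate urticarial rash, and leaves restart after urticaria unsettled

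*Protocol*

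**What the plan says.** The third paragraph of section 8.1.2.2.6 is specific to NVP and describes rash mostly in words rather than grades:

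- Severe rash: "If severe rash OR rash with constitutional symptoms of organ dysfunction OR rash and increased ALT or AST occurs, then permanently discontinue NVP".
- Mild or moderate urticarial rash: "If urticarial rash (mild or moderate) occurs, the subject may continue NVP, but DO NOT reintroduce NVP if it is stopped".
- Severe or generalized urticarial rash: NVP is permanently discontinued.

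The paragraphs that follow mostly work by grade and refer to all study drugs:

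- A held drug: efavirenz or NVP may be held at the investigator's discretion until the skin toxicity settles. NVP held for more than 7 days is then reinstituted with the lead-in dose.
- Grade 3: "For Grade 3 rash, subjects should hold all study drugs". Then: "Upon resolution to Grade <1, the investigator should discuss at a study conference call with senior investigators whether re-challenge is appropriate".
- Grade 4, or any evidence of Stevens-Johnson syndrome: all study drugs are discontinued.
- Grade 2 or 3 rash with any one of several features, including "allergic (e.g., urticaria) symptoms, or is associated with mucosal or target lesions, all study drugs should be held until symptom resolution".

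Three other places bear on this. Section 8.1.4.1 defines holding as temporary and discontinuing as stopping without intent to restart. Section 8.1.4.2.3 says that after an allergic or hypersensitivity reaction "the drug(s) must be discontinued and NOT be re-started". Appendix IV heads its four grade columns "MILD MODERATE SEVERE POTENTIALLY LIFE THREATENING".

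**The concern.** A medical officer who sees a rash in a patient on NVP must decide whether to continue, hold or stop the drug, and later whether it may be given again. For two common descriptions of rash, section 8.1.2.2.6 supports more than one of these answers, depending on the paragraph read. Because the protocol itself separates holding from discontinuing, this is not loose wording: one answer allows the drug to come back and the other does not. At stake are consistent and safe handling of a drug reaction, and a clear record of which regimen the patient was meant to be on.

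**Working it through.** No arithmetic applies, and the protocol gives no figure to reproduce. The check sets the rules side by side after fixing the meaning of the terms.

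**Step 1: terms.** The column labels in Appendix IV make Grade 2 moderate and Grade 3 severe. Its general severity scale also calls Grade 3 severe, described as "Marked limitation in activity, some assistance usually required; medical intervention/therapy required, hospitalizations possible". Section 8.1.4.1 makes a hold reversible and a discontinuation permanent.

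**Step 2: comparison.**

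| Event on NVP | Third paragraph of 8.1.2.2.6 | Later paragraphs of 8.1.2.2.6 | Agree? |
| --- | --- | --- | --- |
| Mild urticarial rash, whether to continue | NVP may continue | Urticaria hold rule starts at Grade 2 | Yes |
| Moderate urticarial rash | NVP may continue | All study drugs held (Grade 2 or 3 with urticaria) | No |
| Severe rash / Grade 3 | NVP permanently discontinued | All study drugs held; re-challenge discussed | No |
| Severe or generalized urticarial rash | NVP permanently discontinued | Grade 3 with urticaria: held until symptoms resolve | No |
| Restart after an urticarial rash | Not allowed once stopped | Hold, then lead-in reinstitution; no urticaria exception | No |
| Grade 4 or any evidence of Stevens-Johnson syndrome | Severe rash: NVP permanently discontinued | All study drugs discontinued | Yes for NVP |

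**Step 3: does the severe-rash conflict depend on equating severe with Grade 3?** Only in part. The Allergic Reaction row of Appendix IV puts generalized urticaria at Grade 3. The third paragraph names generalized urticarial rash and ends NVP permanently. The last rule of the section holds drugs for a Grade 3 rash with urticaria until symptoms resolve. The two meet without any mapping of the bare word severe.

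**Step 4: is NVP exempt from the later rules?** No. The section covers both efavirenz and NVP, the Grade 3 and urticaria sentences refer to all study drugs, and the hold paragraph contains its own NVP lead-in instruction.

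**Step 5: restart.** The third paragraph's ban on reintroduction is written for urticarial rash. Section 8.1.4.2.3 points the same way if urticaria counts as an allergic reaction, as both the last rule of 8.1.2.2.6 and the Allergic Reaction row of Appendix IV suggest. The hold and lead-in rule points the other way. A clinician who obeys the urticaria hold cannot tell whether NVP is paused or finished.

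**The case against.** The best defence is that the rules can be obeyed together. On this view the third paragraph governs NVP, the later rules govern the regimen as a whole, and the Grade 3 discussion concerns only the other drugs. Section 8.1.4.1 does allow a drug to be held during evaluation before a decision to discontinue, and section 8.1.4.2 requires decisions to discontinue or restart to be discussed with the Principal Investigator or a designee. These provisions would limit divergence in practice. But nothing in the text confines the re-challenge discussion to other drugs, and no precedence is stated. A hold that may end in re-challenge is not the same instruction as permanent discontinuation.

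Severe rash in the third paragraph carries no grade, and the section elsewhere uses the phrase for reactions that Appendix IV puts at Grade 4. Equating severe with Grade 3 is therefore the natural reading but not the only one. The generalized urticaria case does not need it.

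Permission to continue is not an obligation, so holding NVP in moderate urticarial rash breaches nothing in the third paragraph. That is correct, but the paragraph still authorises what the later rule tells staff not to do. It can also be argued that a rash associated with urticaria differs from an urticarial rash, and that the Cutaneous/Rash row of Appendix IV does not mention urticaria. The distinction is too fine to guide a decision at the bedside.

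Four stronger readings are tempting, and the document does not support them:

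- **A patient count.** The protocol gives neither the number of NVP starts nor a rate for these kinds of rash.
- **Ambiguity in Stevens-Johnson syndrome.** The instruction to discontinue all study drugs on any evidence of it is explicit.
- **A ban on reintroducing NVP after any rash.** The sentence is about urticarial rash.
- **Damage to a trial outcome.** Section 6.4 defines drug discontinuation as an outcome, but Table 6 does not list it and section 10.2.2.3 states no analysis of it.

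**Conclusion.** The point holds as an internal contradiction in safety management. Severe rash, including severe or generalized urticarial rash, leads both to permanent discontinuation of NVP and to a hold from which the drug may return. Moderate urticarial rash leads both to permitted continuation and to a hold of all study drugs. Restart after urticarial rash is both barred and provided for.

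The severe-rash conflict rests on reading Grade 3 as severe, as Appendix IV does, or on the generalized urticaria overlap alone. The moderate case rests on reading moderate as Grade 2.

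The extent cannot be quantified. Exposure is limited because section 5.2.1.4 bars NVP in women with CD4 above 250 and men with CD4 above 400 when it would be started. Entry requires CD4 above 350, so at entry counts every woman is excluded and only men from just above 350 up to 400 are not. Use becomes more open as counts fall, notably in Step 3 after a CD4 outcome below 250. The intention-to-treat primary analysis and the sample size do not depend on any of this.

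**What to change.** Reconcile the third paragraph of section 8.1.2.2.6, the later paragraphs of that section and section 8.1.4.2.3. A single table by rash grade and type would do it, with one action per drug (continue, hold or discontinue) and one statement on whether restart is allowed. The words mild, moderate, severe and generalized should be tied to Appendix IV grades in the same table. Mucosal or target lesions also need a single entry, because they appear under both the Grade 4 sentence and the Grade 2 or 3 hold rule. The smaller alternative is one sentence stating which passage takes precedence. The clinical leads decide every entry; this review takes no position on which instruction is right.

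The cost is amendment wording and the ethics review that section 11.6 requires. Sample size, visits and analysis do not change.
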